### Intervention development

The intervention web-application consists of five weekly substance-specific modules that provide prevention information geared toward college students. The brief 15-minute web-app modules emphasize simplicity, interactivity, and accessibility. The development of each module’s prevention-related content is guided by evidence-based strategies. The intervention mapping protocol and its collaborative principles were used to develop the web-app [33], in addition to existing needs assessment data from the National College Health Assessment (NCHA) [34], and prior feedback from a pilot Telehealth alcohol program [35].

Diverse stakeholders were engaged following the examination of needs assessment data and the intervention mapping protocol. To develop the content of the intervention, a partnership was formed with a local community-based organization (CBO) specializing in substance abuse prevention and treatment services. Alcohol, tobacco, and other drugs (ATOD) prevention specialists at the CBO created preliminary prevention messages for each substance-specific module including substance-related facts, health risk information, and safe use guidelines from numerous reliable substance abuse sources such as: NIAAA, Centers for Disease Control and Prevention (CDC), American Addiction Centers (Drugabuse.com), National Institutes of Drug Abuse (NIDA), drugabuse.gov, U.S. Food and Drug Administration (FDA), truth initiative, and Generation Rx. A licensed psychologist created short self-assessments for each substance module and developed corresponding feedback. Other stakeholders (i.e., public health Faculty and students, campus recreational center, clubs, campus counseling services) were frequently consulted to provide insight on recommendations for healthy coping strategies/healthy alternative activities, suggestions for improving social wellbeing, and related campus resources accessible to students.

To improve user engagement and information retention, content was delivered using health literacy and health communication strategies [36], such as easy-to-read material, shorter statements, bulleted lists or checklists, and culturally and age-relevant language. Purposeful and relatable photos and graphics were retrieved from open-source platforms such as Creative Commons, Pixabay, and Pexels. Videos that were not created by faculty and students, were sourced from other organizations that allowed for free use, such as Generation RX and ReachOut.com [37, 38]. Content that aims to correct student perceptions of the prevalence of use utilized campus substance use data as reported in the most recent National College Health Assessment [34].

To develop the technical aspects of the web-application, a campus-based web-developer was contracted. During the creation process, web developers met weekly with the study team to discuss design, in-app features, randomization algorithms, and user reminders. The app developers received intended module content and provided mockups to present a visual profile with interactive elements (i.e., quizzes, flip cards, carousels, and videos). They ensured all university accessibility requirements were met, and content was appropriately designed for diverse smart device viewing, usable from either a mobile phone, tablet, or laptop/computer. The application is hosted on a university server and leverages the already existing institutional identification management system, which ensures that participants use their university username and log-in, providing security and confidentiality.

### Theoretical basis

Health behavior theory constructs such as self-efficacy [39] and perceived susceptibility [40], attitudes and subjective norms [41], in combination with individual-level evidence-based substance use strategies including: normative re-education [42], personalized feedback [43, 44], goal setting, and protective strategies [45, 46] are the foundation of the web-app intervention. The substance use prevention modules foster knowledge regarding the health risks associated with substance misuse, perceptions of the prevalence of use, and empower students through refusal skills [47, 48], increase perceived awareness of risks, and describe and outline substance-related coping skills for students to navigate the challenges of college life.

### Intervention modules

The 30-day prevention web-app consists of five weekly substance-specific modules: alcohol, marijuana, nicotine, prescription drugs, and illicit drugs. Each module contains a similar pattern of elements to address the aforementioned health behavior constructs, utilizing evidence-based behavior change strategies and interactive practical applications (see Table 1).

**Table 1 Tab1:** Intervention framework: theoretical constructs, evidence-based behavior change strategies, practical application, and specific outcome measures

Theoretical constructs	Behavior change strategies	Practical application	Outcome measures
**Attitudes/Knowledge**	**Educational content**	- Identify potency, present legal facts via flip cards, quizzlets, videos, etc.	*- Substance-specific knowledge (4 items)* *- Do you ever feel bad about your alcohol or drug use?*
**Perceived susceptibility**	**Correct risk perceptions**	- Define what constitutes risky substance use. - Present health risks of substance misuse and dependency risk via flip cards, quizzlets, videos, etc.	*- What level of risk do you think people have of harming themselves physically or in other ways when they [use a substance]? (6 items)*
**Subjective norms**	**Normative re-education**	- Guess percentage of peer use on campus; show actual vs. perceived use via pie charts. - Inform how college substance use is less frequent than perceived.	*- In the last 30 days, what percent of students do you think used [substance]? (14 items)*
**Self-efficacy**	**Refusal skills**	- Examples of how to say “no” in a variety of scenarios.	*- I would be able to say no if a friend offered me [substance]. (2 items)*
	**Personalized feedback**	- Self-assessment and individualized feedback.	
	**Skills/knowledge for responsible use**	- Responsible use checklist.	
	**Protective strategies**	- Identify healthy alternative activities and support (physical, mind-body, social). - Checklist of healthy study habits. - Links to virtual and on-campus support resources.	
	**Goal setting**	- Write SMART goal for healthy strategies	

First, to address attitudes and knowledge, participants are introduced to each substance through educational facts, such as potency, identification, and effects on the brain and body. Providing a knowledge-based foundation at the beginning of each module supports the formation of positive attitudes regarding substance prevention and negative views of substance misuse and abuse [41, 49]. Next, to apply the construct of perceived susceptibility and correct misperceptions of risk, the module defines risky behavior and identifies potential risks of substance misuse. Additional content is provided on dependency, as well as identifying the health benefits of abstaining from substance use. Recognizing one’s risk for substance abuse and delineating related consequences reinforces intention to reduce or prevent risky substance use [40]. The web-app utilizes a variety of interactive approaches to address these behavior change strategies. For example, to facilitate dissemination of substance-specific knowledge, participants take quizzlets (see Fig. 1), flip content cards, and watch videos. The construct of subjective norms is addressed through normative re-education. Research demonstrates that adolescents and young adults commonly overestimate peer use; and a key prevention approach is to correct such misperceptions [42]. To practically apply this change strategy, the web-app asks participants to estimate the prevalence of peer substance use on campus, then view side-by-side pie charts to compare their “guess” to the “actual percentage” use as confirmed in the campus national college health assessment (See Fig. 2) [34].

**Fig. 1 Fig1:**
[figure not shown]
Example web-app quizzlet to test knowledge content

**Fig. 2 Fig2:**
[figure not shown]
Example side-by-side pie charts to correct misperceptions

The construct of self-efficacy is addressed through five evidence-based behavior change strategies (See Table 1) [39]. The first, personalized feedback, is applied as an in-app short self-assessment on how a participant’s (potential) substance use impacts daily life. In response, an algorithm tailors feedback and if appropriate, encourages students to initiate behavior change. Research demonstrates that strategies such as personalized feedback and self-assessment can significantly reduce substance use and help prevent future use [16, 43, 44]. Providing skills for responsible use, the second self-efficacy change strategy, is applied by highlighting the health rewards of reduced use (or non-use), and displaying responsible use checklists [50]. Refusal skills, the third self-efficacy change strategy, are addressed through examples of how to say “no” in a variety of scenarios. These refusal skills help empower one’s confidence to prevent or reduce substance use in social situations [47, 48], a common occurrence among many college students.

Additionally, each module includes protective strategies to increase self-efficacy. Flip cards with culturally and age-relevant images and language present healthier approaches to stress management and strategies to enhance wellbeing. These healthier approaches underscore the positive effects that strategies, such as physical activity and mindfulness, have on one’s physical, emotional, and mental health [51, 52]. To further demonstrate protective factors, culturally and age-relevant written content is provided on how to establish and strengthen positive social connections and seek out social support, a coping skill found to significantly aid young adults during challenging life events [53, 54]. To facilitate adoption and implementation of these protective behaviors, each module refers students to a web-app tab on the home screen that provides direct resources to access on-campus programs and activities.

Goal setting is the final evidence-based behavior change strategy used to address the construct of self-efficacy. The concluding interactive element of each module encourages participants to write a SMART goal statement to facilitate an action plan for changing risky substance behavior or sustaining responsible use (or non-use). Setting SMART goals (Specific, Measurable, Achievable, Realistic, and Timed) is a significant strategy frequently used in health behavior program planning and intervention development to provide participants criteria on how to create a behavior-specific goal with a well-defined measure for success [55, 56]. Each module provides an example SMART goal for participants to model, such as, “The next time I go out with friends I will order a mocktail instead of an alcoholic drink,” and enables participants to email the goal to themselves if they wish.

### Implementation and evaluation of the intervention

The 30-day iSTART web-app intervention is evaluated through a time series design. The study includes an eligibility screener, a baseline survey, a 30-day exit survey, and a 90-day follow-up survey (see Fig. 3: Schematic of study design). The web-app has been launched at a public university in southern California and is currently undergoing data collection for three years.

**Fig. 3 Fig3:**
[figure not shown]
Schematic of study design

#### Eligibility

Interested students first complete a Qualtrics eligibility screener accessible via the study website. Matriculated students ages 18–30 who identify as low risk for AUD or SUD on the brief DSM-5 criteria screener are eligible to participate, and are redirected to the Qualtrics informed consent and baseline survey. Students who are screened as high risk are referred to additional resources for substance abuse treatment and excluded from the study. Those who agree to participate and complete the baseline survey are subsequently added to the web-app by study staff, and receive an automated welcome email with log-in instructions.

#### Randomization

The web-app is designed to randomize participants to intervention, comparison, or control groups. Upon first login, each participant is automatically randomized into one of the three conditions, and is provided access to the appropriate web-modules: the five weekly substance-specific modules for the intervention group, the single abbreviated module if in the comparison group, or no access to modules if in the control group. The web-application is also designed to keep track of completion dates, or non-completion, and send out automatic reminder emails and new module availability messages to participants.

#### Accessibility

Participants in the intervention and comparison groups can access the web-app on any device that connects to the internet (e.g., smartphone, tablet, laptop, computer). Students can log on using the web-app link embedded in the weekly module reminder email, or directly from the study website. Those in the intervention group have seven days to complete each substance-specific module, and upon completion receive the next module six days later. Those in the comparison group have 30 days to complete the single abbreviated substance module. All participants may contact study staff via email with questions or concerns, and have access to additional study information or support resources (e.g., helplines, treatment facilities, etc.) on the study website. To address any technical errors or server support, study staff communicate with university IT staff directly.

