## Methods

### Study design and setting

The design consists of participant recruitment and randomization of participants to either intervention, comparison, or control conditions with a time series evaluation design. The intervention will occur at a large Hispanic Serving public Institution in southern California. The students in the intervention group will receive a 30-day web-app consisting of five substance-specific modules, while the students in the comparison group will receive a single abbreviated module, and those in the control group will only have access to standard online University substance abuse resources. Study data collection periods consist of a baseline survey after recruitment and assignment to condition, an exit survey after completing the 30-day iSTART web-app intervention (or 30-day comparison or control), and a 90-day follow-up survey.

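### The module release rule does not ensure five weekly modules within the stated 30 days: compliant students take anywhere from 24 to 59 days

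*Protocol article*

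**What the plan says.** All references are to the protocol article.

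- **Duration.** The Abstract gives the intervention as 30 days long. Study design and setting says: "The students in the intervention group will receive a 30-day web-app consisting of five substance-specific modules".
- **Pace.** Intervention modules combines length and pace: "The 30-day prevention web-app consists of five weekly substance-specific modules: alcohol, marijuana, nicotine, prescription drugs, and illicit drugs". Intervention development also describes the modules as weekly, at about 15 minutes each.
- **Release rule.** Accessibility states that intervention students "have seven days to complete each substance-specific module, and upon completion receive the next module six days later".
- **Start of the clock.** Randomization says: "Upon first login, each participant is automatically randomized into one of the three conditions, and is provided access to the appropriate web-modules". The same section says that the app tracks completion dates and non-completion.
- **Exit survey.** Implementation and evaluation of the intervention says: "The study includes an eligibility screener, a baseline survey, a 30-day exit survey, and a 90-day follow-up survey". Study design and setting instead places the exit survey after the web-app has been completed. Incentives pays one sum of $25 for module 5 and the exit survey together.
- **Other arms.** The comparison group has 30 days for its one module, and Study design and setting gives 30 days for comparison and control before exit.
- **Follow-up.** Incentives says that the last survey is sent 90 days after the exit survey is completed.

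**The concern.** The next module is tied to completion of the previous one, so every day a student takes within the permitted window delays all later modules. The stated duration and weekly pace leave no room for this. A student can therefore meet every deadline and still be well short of five modules on day 30.

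At stake are the description of the treatment under test and the comparability of the arms at exit. Either some compliant students are assessed before later modules have been released to them, or the intervention arm reaches exit at a different and more variable time than the other two arms.

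**Working it through.** **Inputs.** Five modules (Intervention modules); up to seven days to complete each, and a six-day lag after completion (Accessibility); module access from first login, taken as day 0 (Randomization); stated length 30 days (Abstract, Intervention modules).

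**Formulas.** Let k be the days used per module, 0 to 7.
- Module m is released on day (m − 1)(k + 6) and completed k days later.
- Course length is five completion times plus four lags: 5k + 4 × 6 = 5k + 24.

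**Can the stated 30 days be reproduced?** Yes, for k of about 1. With k = 1, releases fall on days 0, 7, 14, 21 and 28, which is weekly, and module 5 is completed on day 29. Over the whole permitted range the figure is not reproduced:

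| k (days) | Releases, modules 1–5 (day) | Module 5 completed (day) | Opened by day 30 | Completed by day 30 |
|---|---|---|---|---|
| 0 | 0, 6, 12, 18, 24 | 24 | 5 | 5 |
| 1 | 0, 7, 14, 21, 28 | 29 | 5 | 5 |
| 2 | 0, 8, 16, 24, 32 | 34 | 4 | 4 |
| 4 | 0, 10, 20, 30, 40 | 44 | 4 | 3 |
| 7 | 0, 13, 26, 39, 52 | 59 | 3 | 2 |

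**Thresholds for day 30.**
- All five completed: 5k + 24 ≤ 30, so k ≤ 1.2 on average.
- Module 5 released: 4(k + 6) ≤ 30, so the first four modules must average at most 1.5 days.
- Module 4 released: 3(k + 6) ≤ 30, so the first three must average at most 4 days.

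**Other ways to count.**
- Calling first login day 1 moves every date by one: the range becomes 25 to 60, and k = 1 finishes on day 30.
- Fixed weekly release with a seven-day window ends on day 28 + 7 = 35.
- Counting the six days from release instead of completion ends on day 24 + 7 = 31, or on day 30 if the release day counts as the first of the seven. This comes close, but it sets aside the wording that ties release to completion, and it gives a six-day pace, not a weekly one.

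**Effect on the surveys.**
- *Exit fixed at day 30:* a compliant student with k = 7 is assessed 9 days before module 4 is released (39 − 30) and 22 days before module 5 (52 − 30).
- *Exit triggered by completion:* exit falls at about day 24 to 59 in the intervention arm, against 30 days in the others. If the exit survey is answered at once, the follow-up goes out on day 24 + 90 = 114 to 59 + 90 = 149, against 30 + 90 = 120.

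**The case against.** The best defence is that the rule works as intended for prompt students. The modules are brief, reminders are automatic and module completion is paid. A student who finishes each module the day after release gets exactly the weekly schedule and is done on day 29. That stands: a reader might infer that the rule cannot deliver five modules in 30 days, and this would be wrong. It delivers them to near-immediate completers and does not ensure them for others who are equally compliant.

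A reader might also infer that a null result at exit on prescription or illicit drugs would reflect unopened modules. The article does not support that without two further premises. The exit survey would have to be fixed at day 30, whereas Study design and setting and the joint payment in Incentives point to a survey after completion. And the modules would have to be delivered in the order in which Intervention modules lists them, which no section states.

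Nor can one say what share of students would finish by day 30. The article gives no distribution of completion times, and any such share would follow from whatever distribution was assumed.

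Finally, a condensed article may leave to the full protocol what the app does when a window lapses or a course runs past day 30. That is fair. It does not remove the conflict between a rule and a duration that are both stated here.

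**Conclusion.** The point holds as an internal contradiction. Under the rule as written, a compliant course lasts 24 to 59 days and stays within the stated 30 only if students average 1.2 days or less per module, although seven are permitted. At the slow end, two of five modules are completed by day 30 and two are not yet released. If delivery follows the listed order, those two are the prescription-drug and illicit-drug modules; this is an assumption.

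Which harm results depends on an exit-survey trigger that the article states in two ways: incomplete exposure at exit for some compliant students, or exit and follow-up times that differ between arms. Neither reading yields a uniform 30-day, five-module programme compared at a common time. The range rests on day 0 being first login and on each module being completed within its window.

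**What to change.** Reconcile Accessibility with the Abstract, Study design and setting, Intervention development, Intervention modules, Implementation and evaluation of the intervention, and Incentives, so that the release rule, completion window, stated duration and exit-survey trigger agree. The choice of schedule is the sponsor's. If the present rule stays, the duration should be restated as the 24 to 59 days that it produces.

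In the analysis, use the completion dates that the app already logs to report, for the intervention arm, modules completed by day 30 and by the exit survey. If the exit survey is fixed at day 30, exit results should not be described as the effect of the complete five-module programme.

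The cost is small: a wording correction, or an app setting for students still to be enrolled, and a descriptive table from data already held. Data collection is under way, so this is best settled before analysis. The downside is that, if the rule is kept, the stated duration becomes longer and more variable.

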#### Incentives

Incentives are provided to ensure participation and retention. Participants receive Amazon.com gift cards via email when they complete pre- and post-test surveys and web-app modules. Exit surveys are auto-administered via email from the web-app. The follow-up survey is emailed by study staff to participants 90 days after exit surveys are completed. Participants have two weeks to complete exit and 90-day follow-up surveys. Those in the intervention group receive a total of $100**:** $15 for baseline, $15 for modules 1 and 2, $15 for modules 3 and 4, $25 for module 5 and the exit survey, and $30 for the 90-day follow-up survey. Comparison group participants receive a total of $75: $15 for baseline, $15 for the single module, $15 for the exit survey, and $30 for the 90-day follow-up survey. The control group receives a total of $65: $15 for baseline, $20 for the exit survey, and $30 for the 90-day follow-up survey.

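### The follow-up survey is dated from exit-survey completion, not from randomisation, and the 30-day exit date does not fit the module pacing, so who is measured and when can differ by arm

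*Protocol article*

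**What the plan says.** All references are to the protocol article.

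- **Time zero.** Randomization: "Upon first login, each participant is automatically randomized into one of the three conditions".
- **Exit survey.** Study design and setting places it as "an exit survey after completing the 30-day iSTART web-app intervention (or 30-day comparison or control"). Implementation and evaluation of the intervention lists "a baseline survey, a 30-day exit survey, and a 90-day follow-up survey". Incentives adds that the web-app sends the exit survey automatically by email and that students have two weeks to answer each of the exit and follow-up surveys. It does not name the event or day that triggers the exit email.
- **Module pacing.** Accessibility says intervention students "have seven days to complete each substance-specific module, and upon completion receive the next module six days later". Comparison students have 30 days for one module. Controls have none.
- **Follow-up survey.** Incentives: "The follow-up survey is emailed by study staff to participants 90 days after exit surveys are completed".
- **Exit payment.** For the intervention arm the list reads, in dollars, "25 for module 5 and the exit survey". The comparison arm gets $15 and the control arm $20 for the exit survey alone.
- **Use of the data.** The substance-use outcomes are days of use in the past 30 days. The analysis compares slopes between arms over three waves, and the detectable effects are stated for the final endpoint.

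**The concern.** In a randomised comparison, outcome assessment should be timed from randomisation and attempted in everyone randomised. Here the last assessment is timed from a step that the student takes after randomisation. A missed exit survey leaves the follow-up with no date, so one missed survey can remove both post-baseline waves and all information on that student's slope.

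If exit response differs by arm, the rule carries that difference into the final endpoint. There are reasons why it might. Intervention students work through five modules, comparison students through one and controls through none, and only the intervention arm has its exit payment tied to a module.

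There is a second, related problem. The 30-day label and the pacing rule describe different timetables for the intervention arm, so the article does not settle when that arm's exit survey falls relative to control. The outcome looks back 30 days, so a shift in survey date moves the period being measured.

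**Working it through.** **Inputs.** Day 0 is first login (Randomization), with module 1 taken as available that day. There are five modules, 0 to 7 days to complete each, and 6 days from completion to the next release (Accessibility). The window is 14 days for each survey, and follow-up is sent 90 days after exit completion (Incentives). Let x be the mean days taken per module.

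**The plan's own figure, 30 days.**
- Module 5 released: 4(x + 6). For x = 0 this is day 24; for x = 7 it is day 52.
- Module 5 completed: 4(x + 6) + x = 5x + 24. For x = 0 this is day 24; for x = 7 it is day 59.
- Completion on day 30 requires 5x + 24 = 30, so x = 1.2 days.
- As a variant, a strict calendar-weekly release (days 0, 7, 14, 21, 28) closes the last seven-day window on day 35.

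The 30-day label is therefore reproduced only for students averaging about 1.2 days per module.

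**Reading A: exit follows app completion in the intervention arm and 30 days in control.**

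| Event | Intervention | Control |
|---|---|---|
| Exit sent | day 24 to 59 | day 30 |
| Exit completed (+0 to 14) | day 24 to 73 | day 30 to 44 |
| Follow-up sent (+90) | day 114 to 163 | day 120 to 134 |
| Follow-up completed (+0 to 14) | day 114 to 177 | day 120 to 148 |

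The comparison arm matches control if its exit survey is set by its 30-day period. A control answering on day 30 reports on days 0 to 30. An intervention student answering on day 59 reports on days 29 to 59. The window has the same length in a different position.

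**Reading B: exit sent on day 30 in all arms.** The permitted ranges are then equal: exit completed day 30 to 44, follow-up sent day 120 to 134, completed by day 148. Module 5 is released by day 30 only if 4(x + 6) ≤ 30, so x ≤ 1.5. A student averaging longer than that over the first four modules answers the exit survey before receiving module 5. The follow-up date still depends on when, and whether, the exit survey was completed.

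**Size of a timing effect under reading A (assumed inputs, not in the article).** Suppose use drifts in all arms by 0.05 to 0.20 SD per 30 days, the intervention survey is 5 to 29 days later, and time is coded by wave. The spurious difference runs from 0.05 × 5/30 = 0.008 SD to 0.20 × 29/30 = 0.19 SD. The stated detectable effect for prevention against control is about 0.20.

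**Payments.** Intervention 15 + 15 + 15 + 25 + 30 = $100; comparison 15 + 15 + 15 + 30 = $75; control 15 + 20 + 30 = $65. All three totals agree with the article.

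**The case against.** The strongest reply is that the article never says module completion triggers the exit email. It calls the survey a 30-day survey and gives all three arms a 30-day period. If the email goes out on day 30, the permitted dates are the same in every arm. This stands: a completion trigger is one reading of the design section, and it cannot apply to controls, who have no modules.

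Other points on that side:

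- **Worst case.** Day 59 needs every module finished on its last permitted day, although modules take 15 minutes and reminders are automatic. The control range lies inside the intervention range. This stands: the figures are limits and do not show typical timing.
- **Recall window.** A reader might infer that its length differs by arm. It does not; the same item is used throughout, and only the window's position can move.
- **Exit non-responders.** No sentence excludes them from follow-up, and study staff send that email. That is fair as to intent, but the only stated rule gives them no date. It applies to all three arms, so an inference that data collection depends on adherence in the intervention arm alone is not supported. The dependence can be unequal; it is not confined to one arm.
- **Payment.** Modules 1 to 4 pay $15 per pair, or $7.50 each. At that rate the bundled $25 leaves 25 − 7.50 = $17.50 for the survey, between $15 and $20. The amounts are therefore close, and nothing in the article shows that they alter response. What remains is that the payment is tied to module 5.
- **Modelling.** A mixed model can use actual dates, and time coding may be settled elsewhere. That would reduce the timing problem but cannot recover students who were never surveyed.

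**Conclusion.** The point holds in two parts.

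1. **Follow-up trigger: explicit in the text.** The final assessment is counted from exit-survey completion. As written, missing one survey leaves the student with no date for the next, so the final outcome depends on behaviour after randomisation. Task load and exit payment differ by arm, so the resulting loss can be differential. The article gives no response rates, so its size cannot be estimated.

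2. **Exit timing: an internal inconsistency.** The 30-day label fits the pacing only at about 1.2 days per module. Under reading A the arms can be assessed at different times, with follow-up completed by day 177 against day 148 at the outer limits. Under reading B the dates agree, but any student averaging more than 1.5 days per module is surveyed before module 5 arrives.

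The documents do not support the stronger claim that timing does differ by arm. The spurious difference of 0.008 to 0.19 SD rests wholly on the assumed drift, delay and wave coding.

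A separate wording conflict concerns baseline. Study design and setting describes "a baseline survey after recruitment and assignment to condition", while Eligibility and Randomization put it before first login and hence before randomisation. It does not bear on the timing argument.

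**What to change.** - Send the exit and follow-up surveys to every randomised student on the same fixed days from first login in all arms, whether or not modules or the exit survey were completed. The follow-up could, for example, go out on the exit send day plus 90. With a day-30 exit, follow-up would be sent on day 120 and completed on day 120 to 134 in every arm.
- Invite students already enrolled who missed the exit survey to the follow-up.
- Use actual days since randomisation as the time variable, at least in a sensitivity analysis.
- Pay for the exit survey separately from module 5.
- Reconcile the 30-day label with the design section and the pacing text, and state the exit trigger. Which timetable is right is for the investigators to decide. The choice also determines whether a fixed exit day falls before or after module 5.
- Correct the design section so that baseline precedes randomisation, as Eligibility and Randomization have it.

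**Cost.** A change to the survey emails and a small amendment. The app already records completion and non-completion. The real downside is that data collection has begun, so students enrolled before and after the change would be assessed under two regimes. The analysis by actual days helps to handle this.
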